#### 4.4.2 Withdrawals and missing data

All participants will be included in an intention-to-treat (ITT) analysis, based on their initial group assignment, even if they withdraw or fail to complete the study. For withdrawn participants, their data will still be analyzed as if they completed the study, and missing data will be imputed using the Last Observation Carried Forward (LOCF) method. Only patients with a pre-treatment evaluation and at least one post-treatment evaluation will be included in the analysis.

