Patients will be free to withdraw from the study without having to justify their decision. The principal investigator may end the patient's participation due to loss to follow-up, severe intercurrent pathology, modification/discontinuation of treatment, or change of diagnosis.

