### 2.4 Outcomes

#### 2.4.1 Primary outcome

The primary outcome is the number of patients meeting remission criteria within each post-treatment group. Remission is defined as a MADRS score of 10 or less (Zimmerman et al., 2004) on a scale of 0–60, assessed at the end of 50 iTBS sessions.

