#### 2.4.2 Other clinical and behavioral outcomes

Several clinical and behavioral features will be assessed using:

- the 10-item MADRS total scores to assess depression severity.- the number of responders, defined as those who show a reduction of at least 50% in their MADRS score.- the 13-item Beck Depression Inventory (BDI) (Gould, 1982), to assess self-rated depression.- the 11-item Young Mania Rating Scale (YMRS) (Young et al., 1978), to assess manic states.- the Childhood Trauma Questionnaire (CTQ) (Bernstein et al., 2003) to study early life adversity.- the Chapman Social Anhedonia Scale and the Chapman Physical Anhedonia Scale (Chapman et al., 1976) to investigate respectively physical and social anhedonia.- the Snaith-Hamilton Pleasure Scale (SHAPS) (Snaith et al., 1995) to assess global anhedonia.- the Apathy Evaluation Scale (AES) (Marin et al., 1991) to assess apathy.- the Free-Viewing task (FVT) to assess cognitive biases, more precisely, early and sustained emotional attentional biases.

These outcomes will be assessed before and after the 50 iTBS sessions. The same outcomes will also be assessed at 1 and 3 months after treatment and compared between the two groups. In addition, the relationship between early life adversity and depression severity will be examined, as well as its association with the evolution of depressive symptoms and especially anhedonia.

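### The analysis labelled ITT excludes randomised patients who are never rated after treatment, so it is a modified ITT set, and LOCF can overstate remission at 1 and 3 months

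*Protocol article*

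**What the plan says.** Section 4.4.2 of the protocol article makes three statements about the analysis set and missing data:

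- "All participants will be included in an intention-to-treat (ITT) analysis, based on their initial group assignment", and it extends this explicitly to patients who withdraw or do not finish.
- For those who withdraw, "missing data will be imputed using the Last Observation Carried Forward (LOCF) method". No other method and no sensitivity analysis is given.
- "Only patients with a pre-treatment evaluation and at least one post-treatment evaluation will be included in the analysis".

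The primary outcome (section 2.4.1) is MADRS remission "assessed at the end of 50 iTBS sessions". Table 1 places the MADRS at weeks -1, 0, 2, 6 and 14. On the later ratings, section 2.4.2 says: "The same outcomes will also be assessed at 1 and 3 months after treatment and compared between the two groups". Section 1.2.2.1 makes long-term remission and response secondary objectives.

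Two other rules bear on who is missing. Sections 2.2.1 and 6.6 require treatment to stay unchanged through follow-up. The withdrawal paragraph at the end of section 2.2.1 lets the principal investigator end participation for reasons that include "severe intercurrent pathology, modification/discontinuation of treatment, or change of diagnosis".

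**The concern.** The first and last statements of section 4.4.2 cannot both hold. If a post-treatment evaluation is a condition of entry to the analysis, not everyone randomised is analysed, and the ITT label is wrong. The visit schedule makes this matter for the primary: the first MADRS after baseline is the endpoint itself, so a patient who leaves in the two treatment weeks and does not return has only a baseline score to carry forward, and the last sentence removes that patient. Exclusion then depends on something that happens after randomisation and may differ by arm. Only one arm receives odorants, and section 9 calls patient blinding a major limitation.

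In follow-up the risk is different. A remitter who worsens, has treatment changed and leaves before the next rating keeps the earlier remission at weeks 6 and 14. LOCF also treats carried scores as if they had been observed, which understates uncertainty.

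**Working it through.** **1. The plan's own figures.** Section 2.6.1 requires 74 patients and inflates for 7% attrition: 74 / 0.93 = 79.6, so 80. This reproduces. It implies 80 × 0.07 = 5.6, about 6 randomised patients absent from the primary analysis, which fits the exclusion sentence and not the promise to include everyone.

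The 37 per group does not reproduce at 80% power. With h = 2|asin√0.60 − asin√0.30| = 0.6129, n = 2(1.960 + 0.842)² / h² = 41.8 per group (two-sided 5%). Power at 37 is Φ(0.6129 × √(37/2) − 1.960) = Φ(0.676) = 75%. That is a separate sample-size issue; 75% is used here only as the baseline for comparison.

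**2. Who is excluded.** Reading section 4.4.2 against Table 1:

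| Patient | Treatment under the stated rule |
|---|---|
| Stops sessions, rated at week 2 | Kept, observed score |
| Misses week 2, rated at week 6 or 14 | Kept; baseline carried to week 2. Entry requires MADRS of 20 or more, so in practice a non-remitter |
| Leaves during treatment, never rated again | Excluded |
| Rated at week 2, leaves later | Kept; week-2 or week-6 score carried forward |

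**3. Effect on the primary.** Inputs: 40 per arm, 6 losses, final boundary 0.048 (section 5.1.2). Test: uncorrected chi-squared, z = (p₁ − p₂) / √[p(1 − p)(1/n₁ + 1/n₂)] with p pooled. The splits and remission counts are illustrations chosen near the planned 60% and 30%; all-randomised counts the lost patients as non-remitters.

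| Lost, combined/control | Stated rule, combined vs control | p | All randomised | p |
|---|---|---|---|---|
| 3/3 | 22/37 vs 12/37 (27.0 points) | 0.020 | 22/40 vs 12/40 (25.0 points) | 0.024 |
| 4/2 | 20/36 vs 12/38 (24.0 points) | 0.037 | 20/40 vs 12/40 (20.0 points) | 0.068 |
| 6/0 | 19/34 vs 12/40 (25.9 points) | 0.025 | 19/40 vs 12/40 (17.5 points) | 0.108 |

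For the 4/2 row: 0.2398 / √(0.2454 × 0.0541) = 2.08 under the rule, and 0.20 / √(0.24 × 0.05) = 1.83 with all randomised. Section 4.4.1.2 also allows Fisher's exact test. By that test the 4/2 example is above 0.048 both ways (0.060 and 0.110), while the 6/0 example still crosses (0.034 and 0.168).

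**4. Effect at week 14.** The protocol gives no relapse or follow-up withdrawal rate, so these are assumptions. Take 60% remission at week 2 and 30% of remitters relapsing by week 14: true remission is 0.60 × 0.70 = 42%. If a share q of relapsers leaves unrated, LOCF reports 42% + 0.60 × 0.30 × q: 46.5% at q = 0.25, 51% at q = 0.5, 60% at q = 1. With 20% to 40% relapse and q = 0.5, the overstatement is 6 to 12 points.

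**5. Power with all randomised.** Rates become 0.30 × 0.93 = 27.9% and 0.60 × 0.93 = 55.8%, so h = 0.5741 and power is Φ(0.5741 × √(40/2) − 1.960) = Φ(0.607) = 73%.

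**The case against.** Treatment lasts two weeks, planned attrition is 7%, and all patients receive active stimulation, so few may be lost. With an even split the primary hardly moves. That stands: the problem is sensitivity to uneven loss, and nothing in the protocol says loss will be uneven.

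A reader might infer that the primary is a completer analysis that removes anyone who stops during treatment. The documents do not support this. Exclusion turns on having no post-treatment rating, not on stopping sessions; a patient who stops early but is rated stays in, and one who misses week 2 but returns is kept as a non-remitter.

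A reader might also infer that durability is overstated as a matter of fact, because relapse leads to withdrawal. The withdrawal paragraph is permissive and does not mention relapse, and a patient who relapses and attends is scored as relapsed. LOCF also freezes non-remitters who leave and later improve. The protocol's rules make a link between worsening and missing ratings possible, but they do not establish how often it occurs.

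Finally, counting missing as non-remission is itself an assumption. The uneven examples show that the result depends on how missing patients are handled, not that the all-randomised p-value is the true one.

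**Conclusion.** The contradiction in section 4.4.2 is certain and affects the primary denominator. The set as defined is a modified ITT set. At the planned loss of about 6 of 80 the effect is small if losses are even (27.0 against 25.0 points, no change of conclusion), but an uneven loss can change the conclusion at 0.048: by chi-squared at 4/2, by either permitted test at 6/0. These are illustrations, not predictions.

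For weeks 6 and 14, LOCF can overstate remission and response within an arm. The size rests on assumed relapse and withdrawal rates, and the direction of bias between arms is unknown. This part is less weighty because the outcomes are secondary.

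The analysis set should be settled before the interim look, because section 5.1.2 applies the same analyses there.

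**What to change.** In section 4.4.2:

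- Delete the sentence requiring at least one post-treatment evaluation, and delete LOCF.
- Analyse all randomised patients as assigned. Count a missing MADRS as non-remission and non-response at week 2 and also at weeks 6 and 14, with multiple imputation as sensitivity analysis.
- Analyse repeated scores with the likelihood-based mixed model already listed as an option in section 4.4.1.2, without single imputation.
- State that ending study treatment does not end the ratings already scheduled, unless consent is withdrawn, and reconcile the withdrawal paragraph of section 2.2.1 with section 4.4.2 on this point.

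The cost is a protocol amendment, not only analysis wording, plus some ratings that are already in the schedule. Reported remission rates will be slightly lower. Power is about 73%, against about 75% for the plan's own 37 per arm, so the change costs about 2 points. It should not be read as a fall from the stated 80%; most of that gap is the separate sample-size issue. The cost grows if attrition exceeds the plan: at an assumed 20%, power by the pooled normal formula is 61% with all randomised against 68% for the evaluable set.

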## 5 Methods: monitoring

### 5.1 Data monitoring

#### 5.1.1 Composition of data monitoring committee

The study sponsor will oversee data monitoring and schedule several monitoring visits throughout the study: one after the first inclusion and one annually thereafter.

#### 5.1.2 Interim analysis

Given the pilot nature of this study, we plan to conduct an interim efficacy analysis when 40 patients (50% of the total sample) have been included. This analysis will allow for the earliest detection of the benefit of adding hedonic olfactory stimulation, thus accelerating its availability to patients. During this interim analysis, the same primary and secondary analyses will be performed as at the end of the study. To reduce a type I error (related to α-risk inflation), the spending function of α risk proposed by O'Brien and Fleming (1979) will be used, with a stopping boundary (expressed in *P*-value) set at 0.005 for the interim analysis and 0.048 for the final analysis (Schulz and Grimes, 2005). The study will be stopped if a statistically significant difference in remission rates between the two groups is observed immediately after treatment. No futility analysis is planned.

### 5.2 Harms

Safety assessment will be conducted in accordance with French law. Adverse events attributable to treatment will be verified, assessed and categorized by the principal investigator in the appropriate section of the CRF. This includes any adverse events observed by the investigator as well as any adverse events reported by the participant.

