**Discussion:**

This study may strengthen the development of more effective rTMS interventions and pave the way for the establishment of rTMS combined with olfactory training as a safe, effective, and easily accessible treatment for MDD patients. In addition, this study will contribute to a better understanding of the mechanisms and physiopathology of MDD.

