### 3.4 Blinding

To ensure that patients are blinded to the allocated treatment, the information notice distributed to patients will state that odorants will be diffused during the TMS sessions, but at either a supraliminal or subliminal concentration, meaning that it may be normal not to smell anything. In addition, both the clinicians who complete the clinical scales and the researchers who analyze the data will be blinded to the allocation.

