### 6.3 Confidentiality

All participant-related information will be collected in a paper CRF and reported in an electronic database. The data flow has been declared and approved by the CNIL (National Data Privacy Commission). To ensure confidentiality, all participant documents will be anonymized and will display only an ID code consisting of the treatment group number, serial number and patient initials.

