## 8 Discussion

Thirty percent of individuals suffering from MDD are resistant to pharmacological treatments, underscoring the urgent need for novel therapeutic alternatives to treat depression. rTMS has been proposed as an innovative tool to alleviate depressive symptoms. Although approved by health authorities in certain countries for the treatment of major depression, the considerable heterogeneity in clinical response leaves much room for optimizing its application in clinical settings. Here, we propose the first randomized, double-blind, controlled trial to investigate clinical and biological effects of the combination of hedonic olfactory and brain stimulations.

The iTBS protocol proposed in this study seems to be appropriate, considering that other studies have already shown its efficacy on depressive symptoms (Duprat et al., 2016; Cole et al., 2022; Wilkening et al., 2022), its safety across numerous psychiatric condition (Caulfield et al., 2022; Brunelin et al., 2022) and that accelerated protocols allows a better access to treatment for patients (Mondino et al., 2021). The use of pleasant odorants to modulate neural activity within the reward system is grounded in the close connection between this system and the olfactory one, through structures like the olfactory tubercle. Moreover, stimulation of the left DLPFC is thought to result in the release of subcortical DA (Fonteneau et al., 2018; Brunelin et al., 2011; Strafella et al., 2001), which may help stimulate the reward circuitry.

The knowledge gained from in this project will strengthen the development of more effective NIBS strategy and pave the way for the establishment of NIBS combined with olfactory training as a safe, effective, and easily accessible treatment for patients with both unipolar and bipolar major depressive episode.

In addition, anhedonia can also be considered as a transdiagnostic symptom that is common to psychiatric disorders, including schizophrenia and post-traumatic stress disorder. From this perspective, a similar protocol could potentially be applied to address this symptom across a range of psychiatric conditions.

Finally, this study will provide a better understanding of the mechanisms and pathophysiology of major depressive episodes and depressive symptoms (especially anhedonia), as well as the mechanisms of action of rTMS. Dual-coil TMS, iTBS protocol and fMRI will allow us to better understand the role of the DLPFC in anhedonia.

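### Section 5.2 leaves unclear whether adverse events not attributed to treatment are recorded, so the safety data could depend on a causality judgement that is not stated to be blinded

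*Protocol article*

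**What the plan says.** Section 5.2 (Harms) of the Protocol article has three sentences.

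- The first sets the framework: "Safety assessment will be conducted in accordance with French law". What that law requires is not described.
- The second is the operative rule: "Adverse events attributable to treatment will be verified, assessed and categorized by the principal investigator in the appropriate section of the CRF".
- The third adds: "This includes any adverse events observed by the investigator as well as any adverse events reported by the participant".

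Four other places bear on the point.

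- Section 3.4 says that patients are to be kept blind and that "both the clinicians who complete the clinical scales and the researchers who analyze the data will be blinded to the allocation". The principal investigator, as assessor of adverse events, is not named.
- Section 6.3 says that participant documents "will display only an ID code consisting of the treatment group number, serial number and patient initials". Section 3.3 describes the same code.
- The abstract's discussion says the study may "pave the way for the establishment of rTMS combined with olfactory training as a safe, effective, and easily accessible treatment for MDD patients". Section 8 says, with 'will' in place of 'may', that the knowledge gained will "pave the way for the establishment of NIBS combined with olfactory training as a safe, effective, and easily accessible treatment".
- Section 7.3 states that the manuscript is the full protocol.

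**The concern.** The grammatical subject of the operative sentence is events already judged attributable. On that reading the causality opinion comes before the CRF entry, when it should be one field of an entry made in any case.

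This matters more here than in a trial with an inactive control. Every patient has treatment-resistant depression and every patient receives iTBS; the odorants are the only difference between the arms. For a single patient, nobody can say with confidence whether agitation, poor sleep or headache comes from the illness, the stimulation or the odorant. Randomization answers that question at group level, but only if all events are counted in both arms. A filter applied before recording puts case-by-case opinion in place of the randomized comparison. No analysis plan written later can restore events that were never entered.

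Section 5.1.2 adds some weight. It allows the trial to stop for efficacy at an interim analysis once 40 patients are included, which at 1:1 allocation is about 40 / 2 = 20 per arm. With so few patients, complete capture of events matters more.

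**Working it through.** No figure in the document bears on this point, so there is none to reproduce. The check is one of reading, plus a short piece of algebra.

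**1. Is section 5.2 the only rule?** Section 2.4 lists no adverse-event outcome, Table 1 has no adverse-event row, and section 4.4 does not mention adverse events. Section 5.2 therefore stands alone on which events are captured. That is a data-collection rule, not an analysis detail.

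**2. What does it require?** Two readings are possible.

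- *Attribution is a condition for entry.* The operative sentence speaks only of attributable events, and the next sentence opens by referring back to them. On this reading it lists who may be the source of such events (investigator or participant) and leaves the condition in place. This is the more natural reading.
- *Everything is entered.* The third sentence uses 'any' twice, and attribution may describe only what the principal investigator goes on to assess. This reading is possible.

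The text does not settle the matter. Two people completing the CRF in good faith could follow different practices.

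**3. What follows if attribution is a condition?** Let p be the true proportion of patients with an adverse event in an arm, and a the proportion of those patients who have an event judged attributable and so recorded. Write C for the combined arm and A for iTBS alone.

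- Recorded proportion in an arm = p × a.
- Recorded difference = p_C × a_C − p_A × a_A.
- If everything is recorded, a_C = a_A = 1 and the difference is p_C − p_A.
- If a_C = a_A = a < 1, the difference shrinks to a × (p_C − p_A).
- If a_C and a_A differ, the difference can shrink, vanish (when a_C / a_A = p_A / p_C) or grow.

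The filter is harmless if every individual attribution is correct, because then only background events are removed. The design gives no means of checking that. The document gives neither p nor a, so any numerical example would rest wholly on assumed rates, and none is offered.

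**4. Is the attribution protected by blinding?** Section 1.3 calls the trial double-blind, and section 3.4 names patients, scale raters and analysts. The role that attributes events is not on that list. The participant code carries a group number, though the text does not say whether that number reveals the treatment. The supported statement is that blinding of this judgement is not stated.

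**5. What is claimed about safety?** Both passages are forward-looking: 'may' in the abstract, 'will' in section 8. Both concern the combined treatment. Neither is tied to a safety objective, hypothesis or test.

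**The case against.** The strongest reply is that section 5.2 never says that non-attributed events go unrecorded. It refers to any event observed or reported and places safety under national law, whose recording duties cannot be seen here. Causality assessment by an investigator is routine and does harm only if it decides what is recorded. That much stands: exclusion is a likely reading, not an established fact. It does not remove the point, because a rule that allows both practices needs rewording.

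A reader might infer more than the documents support:

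- *That a conclusion of safety for the odorants is planned.* The wording expresses a hope for the combination, and no safety objective or test is stated.
- *That the principal investigator is unblinded.* No section says so. The trial is declared double-blind, section 3.2 keeps the sequence from those enrolling and allocating, and the principal investigator might be one of the blinded raters.
- *That worsening mood or suicidal thoughts would be lost.* Blinded clinicians rate the MADRS at weeks 2, 6 and 14 as well as at baseline (Table 1), and section 4.4.1.2 compares depression severity by group and time. Such worsening is therefore partly captured without any attribution. Events outside the scales, or between those visits, are not.
- *That the lack of a by-arm adverse-event table is a defect.* Such tables commonly sit in an analysis plan, which is not shown here, so this is not counted.

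**Conclusion.** The point holds as one of unclear and badly fixed wording. Taken literally, section 5.2 makes attribution a condition for entry; the sentence after it leaves open whether other events are recorded; and the role making the judgement is not stated to be blinded. If attribution does filter entry, a between-arm comparison of harms would depend on that judgement, and the data would only weakly support calling the combined treatment safe.

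The conclusion rests on two things: that the literal reading could be followed in practice, and that attribution in individual patients is imperfect. Its size cannot be stated from the document. It does not touch the remission endpoint or the depression ratings. The wording should be settled while events are still being collected, because unrecorded events cannot be recovered reliably afterwards.

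**What to change.** Reword section 5.2 to say that all adverse events in both arms, observed or reported, are recorded in the CRF whatever their suspected cause. Make relation to treatment a separate field, completed after the event is entered and judged blind to group where possible. Keep the word 'safe' in the abstract and section 8 to what those data show.

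The cost is a change to protocol and CRF wording, with no new visits. The downside is that more minor, unrelated events will have to be recorded.
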